### Recruitment {15}

The research team already has good collaboration networks with municipalities and schools in Chile. Strategies to achieve adequate school enrolment to achieve the target sample size will consist of contacting and presenting to the municipal study authorities who are expected to help establish contact with school authorities. In addition, research assistants will communicate directly and inform school authorities about the study’s purpose, requirements and duration.

## Assignment of interventions: allocation {16}

### Sequence generation {16a}

Schools will be randomly distributed to either group with an allocation ratio of 1:1 through an automated procedure using Excel (Microsoft) and the command “RAND”. A statistician independent of the research team will perform the randomization.

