**Methods:**

A cluster-randomized controlled trial design will be used. A tablet-based video game that stimulates cognitive and socio-emotional skills to improve the development of academic skills is compared with a tablet-based game where students draw and paint with no explicit stimulation of cognitive and socio-emotional skills. Eighteen schools and 750 Chilean preschool students will be recruited. The effectiveness of the intervention will be assessed using a direct evaluation of children on literacy learning and pre-calculation skills at baseline, immediately after stimulation, and at 6, 12, 18, and 24 months post-intervention. The mediating effect of working memory, inhibitory control, emotion recognition, and prosocial behaviours will be assessed on the effectiveness of the intervention.

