## Methods: participants, interventions, and outcomes

### Study setting {9}

This study will be carried out in schools with preschool education located in two cities in the Maule region (Talca and Linares), Chile.

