### Sample size {14}

To determine a significant difference (alpha =0.05) in the measure of the primary outcome (academic skills: early literacy/precalculus), between the comparison and intervention groups, with a power of 80%, we need to recruit six schools with a total of 264 students per group, with an average of 44 students per school (distributed in two courses). For the sample calculation, the Stata statistical package was used, and the “clustersampsi” command, which indicates the differences between groups concerning an average score and considers the correlation effect between the subjects within the same school through the intracluster correlation coefficient (ICC = 0.02) [11]. The information to feed this equation was extracted from a previous study [37], where the control group in the early literacy variable post-intervention measure had a score of 20.06 (DS = 8.32). Assuming a difference in favour of the intervention group of 0.4 DS, the sample size was calculated for this study. In addition, it is estimated that 10% of eligible students might not want to participate, and estimating a 20% loss in follow-up, each group should initially recruit 377 students. This implies that four extra schools will be recruited per group, totalling 16.

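### Few schools from two cities are allocated with no stated stratification by city, and city is not in the primary model: a minor point that is cheap to fix

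*Protocol article*

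**What the plan says.** Sequence generation {16a} describes the allocation: "Schools will be randomly distributed to either group with an allocation ratio of 1:1 through an automated procedure using Excel", with the RAND command, carried out by a statistician independent of the team. Concealment mechanism {16b} and Implementation {16c} say who is told and how, and add no restriction. The stratification option mentioned under Statistical methods {20a} belongs to the Mplus mediation models, not to allocation.

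The schools are "located in two cities in the Maule region (Talca and Linares), Chile". Their number is not consistent. The abstract says "Eighteen schools and 750 Chilean preschool students will be recruited". Sample size {14} says "This implies that four extra schools will be recruited per group, totalling 16", although six plus four per group makes 20.

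The primary mixed model in {20a} accounts for clustering by school and adjusts for gender, age, mental health and the same test at baseline. City and the school vulnerability index are not listed. The index must be known before allocation, because it is an entry criterion for schools under Eligibility criteria {10}.

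**The concern.** When whole schools are randomised and there are only 8 to 10 per arm, one draw can leave the two cities unevenly spread over the arms. The city of each school is known beforehand, so this can be prevented, yet it is neither used in the allocation nor adjusted for.

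The baseline test takes up most of any difference between the cities in starting level. It cannot take up a difference that opens later, for example through teaching or through the school closures that the Discussion names as a risk. Follow-up runs to 24 months and into first grade. In a lopsided draw, part of such a difference would appear as an effect of the game, and the team would have to defend a split that it could have avoided.

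**Working it through.** **The plan's own figure.** Inputs from Sample size {14}: difference 0.4 SD, alpha 0.05 (taken as two-sided), power 80%, ICC 0.02, 44 children per school.

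- Individual randomisation: 2 × (1.960 + 0.842)² / 0.4² = 98.1, so 99 per arm.
- Design effect: 1 + 43 × 0.02 = 1.86. Then 99 × 1.86 = 184 children, or 4.2 schools of 44.
- With a t distribution on 2(k − 1) degrees of freedom, 5.1 to 5.4 schools are needed, rounded up to 6. This reproduces "we need to recruit six schools with a total of 264 students per group, with an average of 44 students per school".
- Losses: 264 / 0.70 = 377. Then 377 / 44 = 8.6, so 9 per arm, which fits the 18 schools of the abstract. Because the count is unsettled, 16, 18 and 20 are all carried below.

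**City mix.** Let N schools be split equally, with m in the smaller city and x of those in one arm. Then x is hypergeometric, and the gap in city mix is |2x − m| / (N/2). The article does not give m. I assume about a quarter, a third or a half of N, in whole schools.

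| N | m | P(gap of 40 points or more) |
|---|---|---|
| 16 | 4 | 7.7% |
| 16 | 5 | 2.6% |
| 16 | 8 | 13.2% |
| 18 | 4 | 8.2% |
| 18 | 6 | 13.1% |
| 18 | 9 | 5.7% |
| 20 | 5 | 3.3% |
| 20 | 7 | 5.7% |
| 20 | 10 | 17.9% |

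The range is about 3% to 18%. It moves unevenly because with so few schools only certain gaps can occur. For N = 18 and m = 6, the event is a 5:1 or 6:0 split: 2 × (220 + 2,970) / 48,620 = 0.131.

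**What a lopsided draw would do.** A 5:1 split with 9 schools per arm is a gap of 5/9 − 1/9 = 0.44. If the cities drift apart after baseline by 0.1 to 0.3 SD (an assumption), the estimate from that draw shifts by 0.44 × 0.1 = 0.04 to 0.44 × 0.3 = 0.13 SD, against a target of 0.4 SD.

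**Starting level.** The SD of the difference between arms in baseline mean is √(2 × (ICC + (1 − ICC)/44) / k). At ICC 0.02 it is 0.10 SD for k = 8 and 0.09 SD for k = 10. A gap above 0.2 SD then has a probability of 5.2% (16 schools), 3.9% (18) or 3.0% (20). At an assumed ICC of 0.10 the range is 20% to 25%.

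**Effect on the planned analysis.** Simulation of baseline-adjusted school means with 18 schools, 6 of them in the smaller city, 6,000 runs per setting. Assumed: baseline–outcome correlations of 0.7 (child) and 0.8 (school), a city gap of 0 to 0.4 SD, and city not in the model.

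| ICC | Allocation | SD of adjusted effect | Type I error | Power for 0.4 SD |
|---|---|---|---|---|
| 0.02 | unstratified | 0.065–0.069 | 4.6–4.8% | at least 99.9% |
| 0.02 | by city | 0.065–0.068 | 4.4–5.4% | at least 99.9% |
| 0.10 | unstratified | 0.104–0.108 | 4.8–6.1% | 93–94% |
| 0.10 | by city | 0.103–0.105 | 4.4–4.9% | 94% |

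Monte Carlo error on type I error is about 0.6 points. Bias was near zero throughout. The simulation has no separate scenario for a city difference that opens only after baseline.

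**The case against.** The strongest reply is that valid randomisation needs no balance. Chance imbalance is not bias, the standard error already allows for it, and the simulation finds almost no gain from stratifying. This stands, and it limits the point to a small one.

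The 0.3 SD city difference is also generous. With 12 schools in one city and 6 in the other, it implies a between-school variance of (1/3)(2/3)(0.3²) = 0.02, which is all that an ICC of 0.02 allows. The common entry criteria narrow the differences between schools further. The primary time point also comes right after a programme of two and a half months, which leaves little room for the cities to diverge. The argument about later divergence therefore applies mainly to the follow-ups. These limits stand too.

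A reader might infer that RAND acts as a coin flip for each school, so that the arms could turn out quite unequal, or that the list cannot be audited because RAND recalculates. The article does not support either reading. It states a 1:1 ratio, which sorting on RAND and cutting the list in half delivers. How the output is frozen and filed is operational detail that an article may leave out. A restriction could likewise stand in a fuller document. What remains is that the section goes down to the spreadsheet command and names none, and that city is missing from the listed covariates.

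**Conclusion.** The point holds as a minor design improvement. City is known in advance, the schools are few, and neither the stated allocation nor the primary model uses it. A gap of 40 points or more in city mix has a chance of about 3% to 18%, given equal arms and a quarter to a half of the schools in the smaller city.

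A reader might go further and conclude that an imbalance is likely enough to compromise the comparison. The documents do not support that. At the plan's own ICC, a baseline gap above 0.2 SD has a chance of 3% to 5%. The planned model adjusts for the baseline test, simulated type I error stays near 5%, and the loss of power without stratification is about one point or less even at ICC 0.10. The shift of up to 0.13 SD needs both an unlucky draw and an assumed city difference that the baseline scores do not capture.

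The conflict between 16, 18 and 20 schools is a separate inconsistency that should be reconciled in its own right.

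**What to change.** In Sequence generation {16a}, state that the independent statistician allocates schools 1:1 within each city, with arm sizes as equal as possible. Schools may also be ordered within city by the vulnerability index already collected for eligibility. If both cities have an odd number of schools, the extra school goes to opposite arms. The gap in city mix is then at most one school per arm (1/9, or 11 points, with 18 schools) and zero when both numbers are even. In Statistical methods {20a}, add city as a fixed effect in the primary model.

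The cost is one degree of freedom at school level (15 instead of 16 with 18 schools) and very little of the statistician's time. No new data are needed. If the schools have already been allocated, only the covariate can still be added, and this should be fixed before the data are unmasked.

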### Concealment mechanism {16b}

After the randomization and allocation, schools will be informed by a research assistant of the group belonging by email and confirmed by telephone. Each school will only receive their information of allocation. Additionally, this information will not be disclosed to the assessment research team (outcome evaluators) to keep them blind to the schools’ allocation.

### Implementation {16c}

An independent statistician will perform the randomization to assign to the study arms, and this statistician will give this information to a research assistant. Later, the research assistant will inform schools by email and confirm by telephone.

## Assignment of interventions: blinding

### Who will be blinded {17a}

This is a double-blinded trial, blinded to the outcome evaluators and the data analyst. Outcome evaluators will not be informed about the group of belonging and will be instructed not to ask the students or the school authorities about the school's condition. A data analyst will work with the final dataset, where the group condition will be masked.

### Procedure for unblinding if needed {17b}

For the nature of the intervention, the participants will know the allocation of the school.

## Data collection and management

### Plans for assessment and collection of outcomes {18a}

Each participant will be evaluated individually on six occasions, one before the intervention and five after the intervention, using the tasks focused on working memory, inhibitory control, emotion recognition, choice of prosocial behaviours and precalculus skills and early literacy, in 2 sessions lasting approximately 40 minutes each (with breaks in each). Trained psychologists will conduct the children’s assessment in a 1:1 ratio. Each trained psychologist will arrange the evaluation time during school hours, which will occur in a pre-determined location on the school premises. The conditions for the evaluation will be ensured: privacy, no distractions, and safety. The trained psychologist will be responsible for the well-being of the children in the assessment, and a supervisor may be in place or on call for any support if needed. To ensure data quality recollection, evaluators will fulfil a daily report of incidents with the children, and a supervisor will solve the problems. In addition, the supervisor will make field visits to check if these assessments follow the evaluation protocol. On the other hand, the parents will answer a mental health questionnaire of the child during the periods of the children’s assessments. The instruments to be used in the measurements are described below.

### Plans to promote participant retention and complete follow-up {18b}

To ensure greater rigour in the research design, a record of the children’s attendance and percentage of participation of the children in each session will be made (for both groups: intervention and comparison). An observation record will be kept, made by a member of the research team, of each session carried out, where the number of children who are playing will be recorded every 5 min, and the reasons why the children are not performing the task will be noted (e.g. went to the bathroom, a problem with the tablet). In addition, the observation protocol will include multiple-choice items that will try to capture the main difficulties encountered during the programme implementation and how the educator and the assistant are responsible for supporting the children during the session to carry out the activity. Students will not have access to the software between sessions.

### Data management {19}

After the participants have completed the questionnaires, the data will be entered into a secure platform without identifying information (each participant will be assigned an encrypted ID number). The original copies of the instruments will be filed and stored, under lock and key, in a self-storage, along with the list linking the participants’ names and ID numbers. Only the principal investigator, research assistants in charge of data entry, and the statistician will have access to the database.

### Confidentiality {27}

Research data will be stored using a study identification code for each participant. The key to the identification code list will only be available to the research team mentioned above. It will be documented and safeguarded according to research guidelines after the completion of the study. No participant identification details will be reported in publications or any study report.

### Plans for collection, laboratory evaluation, and storage of biological specimens for genetic or molecular analysis in this trial/future use {33}

Not applicable. There are no biological samples in this assay.

## Statistical methods

### Statistical methods for primary and secondary outcomes {20a}

First, descriptive analyses will be performed to evaluate the balance of variables between groups at the beginning of the study. The primary analysis will be conducted based on intention-to-treat. This analysis includes all randomized subjects in the groups, regardless of whether or not they complete the treatment or follow-up period. Multivariate regression models of mixed effects will be carried out considering as a dependent variable the performance in the tests of academic skills (initial literacy and precalculus) and as an independent variable belonging to the intervention or comparison group, controlling for gender, age (in months), mental health, and performance in the same tests in the baseline evaluation. Regression models will consider the nested nature of the data (clustering), since students’ performance within the same educational establishment tends to be correlated. While primary outcomes will be considered as those obtained after the intervention, analyses will be repeated for follow-up at 6, 12, 18, and 24 months. This will allow for evaluation of the maintenance of the effect of the intervention until first grade. We will use mixed-effect regression models of repeated measures to assess convergence and divergence between groups in follow-up times. Subgroup analyses will be performed for the primary outcome variable using interaction terms in the regression models between the randomized groups and the gender variable. This will allow us to evaluate the moderating effect. Sensitivity analyses will also be performed to assess the impact of lost data using multiple imputations. The results with and without imputed data will be presented and compared. The tests will be done with Stata 15.0.

Finally, multilevel models of mediation will be adjusted using Mplus 6, entering all the hypothesized mediators simultaneously: working memory, inhibitory control, recognition of emotions, and choice of prosocial behaviours. We will calculate the effect of the intervention on each mediator, the effect of each mediator on the primary outcome, and the effect of the intervention that each mediator mediated. For each model, we will calculate the intervention’s indirect effects and the unique indirect effect for each mediator. Then, we will calculate the direct effect of the programme. Because randomization will be at the school level, we will understand the school as second-level and individuals as first-level. To control variability across schools, we will use the Mplus stratification option. Then, we will separate the models for initial literacy and prequel skills. All models will be adjusted for gender, mental health, and values of the mediating variables in the baseline evaluation. Covariations between all variables within time will be allowed.

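### The mediation plan makes school the second level but then handles school variability by stratification; the two do not fit together, and with school as stratum only, the intervention paths would be tested with too small an error term

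*Protocol article*

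**What the plan says.** In the protocol article, the mediation paragraph of Statistical methods for primary and secondary outcomes {20a} states that "multilevel models of mediation will be adjusted using Mplus 6", with the four hypothesised mediators entered together. The quantities of interest begin with this: "We will calculate the effect of the intervention on each mediator, the effect of each mediator on the primary outcome". The indirect effects and the direct effect follow.

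On the school level, two consecutive sentences apply. The first reads: "Because randomization will be at the school level, we will understand the school as second-level and individuals as first-level". The second reads: "To control variability across schools, we will use the Mplus stratification option". The paragraph names neither a cluster variable nor a stratification variable, and does not say how the two statements combine.

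Sequence generation {16a} gives the unit of allocation: "Schools will be randomly distributed to either group with an allocation ratio of 1:1". It describes no stratified randomisation, so the article names no design stratum to which the option could refer.

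**The concern.** Stratification treats the strata as fixed and computes sampling variance within them, so differences between strata do not enter the standard error. That suits a true design stratum. It does not suit the randomised unit.

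Here every child in a school has the same arm. The contrast between arms is a contrast between sets of schools, and school-to-school variation is part of its error term. If schools are declared as strata and nothing else is done, that part is lost for the intervention-to-mediator paths and the direct effect. The mediator-to-outcome path is mainly a within-school relation and is much less exposed. Indirect effects are touched only through their first leg.

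Mediation is specific objective (d) and a stated hypothesis. Four intervention-to-mediator paths are to be estimated, in separate models for literacy and precalculus. A raised error rate on those paths could give a false account of how the game works.

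**Working it through.** **Inputs.** From Sample size {14}: ICC 0.02, 44 children per school, alpha 0.05 (taken as two-sided), difference 0.4 SD, 80% power, 10% non-participation and 20% loss. The ICC is given for the academic outcome. The article gives none for working memory, inhibitory control, emotion recognition or prosocial choice, so using 0.02 for the mediators is an assumption.

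**The plan's own figure.** The article gives no error rate for the mediation model. The nearest figure is the sample size, which rests on the same ICC and cluster size.
- Individual randomisation: 2 × (1.96 + 0.84)² / 0.4² = 98.1, so 99 per arm.
- Design effect: 1 + (44 − 1) × 0.02 = 1.86. Then 99 × 1.86 = 184 per arm, or 4.19 schools by the normal approximation.
- With t quantiles on 2(k − 1) degrees of freedom, k = 5 requires 5.39 schools and k = 6 requires 5.10, so six schools and 6 × 44 = 264 children.
- Recruitment: 264 / 0.70 = 377.

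These agree with the stated six schools, 264 and 377 per group.

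**Readings of the stratification sentence.**

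1. *School is stratum only.* For a school-level contrast, the correct variance is proportional to 1 + (m − 1) × ICC and the within-stratum variance to 1 − ICC. The correct standard error therefore exceeds the computed one by R = √{[1 + (m − 1) × ICC] / (1 − ICC)}, and the actual two-sided error is 2 × [1 − Φ(1.96 / R)].
 - m = 44, ICC 0.02: R = √(1.86 / 0.98) = 1.38; error 15.5%.
 - m = 44 × 0.70 = 30.8, ICC 0.02: R = √(1.596 / 0.98) = 1.28; error 12.5%.

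 Other ICC values, all assumed:

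 | ICC | 30.8 per school | 44 per school |
 |---|---|---|
 | 0.01 | 8.7% | 10.3% |
 | 0.05 | 22.6% | 28.2% |
 | 0.10 | 35.1% | 41.9% |

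 A simulated null intervention-to-mediator path (20,000 trials per setting, 44 per school, ICC 0.02; 6, 8 or 9 schools per arm) gave 15.6% to 15.9%, in line with the formula.

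2. *School is both stratum and cluster.* Each stratum then holds one cluster. A variance between clusters within a stratum needs at least two, so it cannot be estimated.

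3. *School is the level-2 cluster and stratification is not used for it.* Between-school variance stays in the error term. The same simulation gave 6.9% to 7.9% with a normal reference, and 4.9% to 5.2% with a t reference on 2k − 2 degrees of freedom (k schools per arm).

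4. *Some other variable, such as city, is the stratum.* The article names none, and a city stratum would not serve the stated purpose of controlling variability across schools.

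The range of 6 to 9 schools per arm covers the calculated six and half of the stated totals of 16 (Sample size) and 18 (Abstract). Those totals do not agree with each other, which is a separate matter.

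**The case against.** The strongest defence is the sentence just before. It makes school the second level and gives randomisation by school as the reason. If that model is fitted, between-school variance is kept and reading 1 never occurs. The stratification variable is also not named, and exact software syntax is detail that an article may leave to the full protocol or analysis plan. This stands to the extent that a reader might infer that the mediation tests will be anti-conservative, and the article does not support so firm a conclusion. It supports only a conditional one.

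The defence does not rescue the sentence itself. Choosing stratification to deal with school variability is a stated method, not an omitted detail, and none of the four readings lets it stand unchanged.

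Three further limits also stand:
- The ICC of 0.02 is borrowed from the academic outcome. The models adjust for baseline mediator values, so the relevant ICC is a residual one that the article does not give.
- A reader might carry the 12% to 15% over to the indirect effects. The calculation concerns a single intervention path, and no error rate was computed for an indirect effect.
- A reader might take the trial's main result to be at risk. The effectiveness analyses are mixed models that account for clustering by school and do not use this option.

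**Conclusion.** The point holds as an internal inconsistency with a conditional consequence. The mediation paragraph treats school as a level-2 unit and also assigns school variability to a stratification option. The sentence on stratification needs to change under every reading.

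The inflation from a nominal 5% to about 12% to 15% applies if school is stratum and not cluster. It assumes a mediator ICC of 0.02, 31 to 44 children per school and a two-sided test, and it concerns the intervention-to-mediator paths and the direct effect. The matter is confined to objective (d).

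**What to change.** Replace the stratification sentence with: *School is the cluster (level-2) variable in a two-level model, with intervention entered at the school level.* Drop the stratification option. Add that intervention paths are tested against a t reference on the number of schools, or an equivalent small-sample method, since naming the cluster correctly does not by itself bring the error to 5% with so few schools.

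If fitting one mediator at a time is considered as a fallback for non-convergence, it should either be left out or be labelled as a departure: it no longer gives the unique indirect effect of each mediator that the simultaneous model is meant to estimate.

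The cost is one rewritten sentence, one added sentence and a different syntax line. No data collection or design feature changes. Compared with a stratum-only analysis, intervals for the intervention paths will be wider.
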